## Objectives

This feasibility study is undertaken in preparation for RCT to explore uncertainties and enable us to optimize the intervention or the conduct of the trial. Thus, the primary objective is to determine the feasibility of outcome data collection with this systematically adapted PFA training intervention to the target population and obtain preliminary estimates of variability in participants outcomes, which could inform future sample size estimation for an RCT. The secondary objective is to generate the acceptability of this training intervention. Meanwhile, a nested process evaluation using qualitative methods will be conducted from diverse perspective in parallel to extend the acceptability and feasibility for randomized trial, as well as provide a comprehensive contextual information about potential barriers and facilitators related to PFA training intervention implementation. All detailed study objectives can be found in Table 2.

**Table 2 T2:** Study objectives: Feasibility and acceptability.

**Domains**	**Research questions**	**Methods**	**Participants**
**Primary objectives: Feasibility**			
1-1 Recruitment and retention	• Can numbers of frontline healthcare workers be adequately recruited, trained, and retained for outcome analyses?	• Process outputs: trainees (number available in wards, number at training, number at supervision sessions; number completing measurement tools and time 1, 2 and 3)	Trainees
1-2 Adherence	• How many participants attend training sessions/supervision sessions? • What are the reasons for failing to attend training and supervision sessions?	• Attendance record for training and supervision sessions • Observation fieldnotes of training and supervision sessions • Qualitative interviews with expert trainers, and trainees	Trainees, trainers
1-3 Feasibility of measurement tools	• Are the assessment tools acceptable to participants for collecting training outcomes? • Are the measurement tools sensitive to assess the changes?	• Measurement tools completion rate, time for completion, number of missing items • Qualitative interview with participants about appropriateness of outcomes measures	Trainees
1-4 Overtime changes	• Do healthcare trainees' knowledge, attitudes, skills, well-being change after training, and is this sustained at follow up?	• Outcome's assessment pre-and post- training, plus 1- and 3-months follow-up • Calculation with mean score and standard deviation over time	Trainees
**Secondary objectives: Acceptability**			
2-1 Program evaluation	• Did attending training and supervision lead to trainees' improvement in practice, if so, what were these? • What do trainees think about PFA training program and supervision sessions?	• Qualitative interviews with trainers, trainees, and clinical ward manager think about the PFA training (is the format acceptable, is there anything missing, likes and dislikes, barriers, and challenges to complete the training and supervision) • Observation fieldnotes from training and supervision sessions	• Trainer, trainees, clinical ward manager
• 2-2 Fidelity of training intervention	• Did the trainers deliver the training as intended?	• Analysis of observation fieldnotes and transcripts of training session video recordings. Researcher rated PFA training intervention using a fidelity assessment tool.	• Trainer

## Methods and Analysis

### Design

Given the implementation of PFA training intervention involves several components, including target a range of the behaviors, the trainers need mental health expertise and those receiving the intervention are experienced frontline healthcare workers, it can be described as a complex intervention. This study design has considered the Medical Research Council (MRC) framework, which is particularly suited to guide the adaptation and assessment of the feasibility/acceptability, with the intention of improving the design and evaluation, thereby to achieve an ultimately effective, sustainable, and scalable training intervention (53). Followed the guidance, this study protocol describes two steps of (A) feasibility trial evaluation following the recommendations of the SPIRIT 2013 statement [Standard Protocol Items: Recommendations for Interventional Trials] (54) and (B) process evaluation. The study flowchart is displayed in Figure 1.

**Figure 1 F1:**
[figure not shown]
Study flowchart.

#### (A) Feasibility Randomized Controlled Trial

A two-arm, feasibility randomized control trial will be used to test an adapted PFA training in a Chinese population of frontline healthcare workers. The purpose of the feasibility trial is to achieve two objectives (1) to determine the acceptability and feasibility of outcome data collection; and (2) to generate preliminary estimates of variability in trainee outcomes, which can inform sample size estimation for a large-scale RCT.

#### (B) Process Evaluation

Qualitative research will follow to add the feasibility and acceptability of this adapted PFA training intervention in a large tertiary hospital setting to complete interviews and observations with trainees as well as their clinical ward manager and trainers. Those generated potential contextual information about this feasibility RCT from multiple stakeholders will help to inform future intervention refinements and study design (55, 56).

### Feasibility Randomized Controlled Trial

#### Setting

The recruitment of participants and implementation of the “Preparing Me” PFA training intervention will be conducted in a representative Chinese tertiary hospital (The Second Xiangya Hospital of Central South University) in Hunan Province, the central part of China.

It has been selected because of the following three characteristics: First, this is a designated emergency response hospital in China that they have established a national emergency medical rescue team which has been approved by the National Health Commission of the People's Republic of China in 2012. Within China's four-tier response system for public health emergencies that determines what measures a region will implement, with level I the most serious, every designated regional medical institute will take on the responsibility of emergency medical rescue accordingly. Generally, the approved national rescue team will be called out not just national major public health emergency but also regional rescue services. Therefore, as a representative emergency response center, healthcare workers working in this hospital are regularly serving the role of responding to natural disasters, infectious disease outbreaks, and other critical incidents at all levels. According to the hospital administration data, healthcare workers have been dispatched by national authorities to provide emergency rescue services on 80 different occasions for a range of natural, social security, and public health emergencies during the past 7 years. These include national major emergencies (e.g., Ya'an earthquake in 2013, Sinking of Dongfang zhi Xing in 2015, Tianjin Explosion in 2015, Wuhan first wave of COVID-19 pandemic in 2020) and regional emergencies (e.g., Yiyang Floods in 2018, Changde car accident in 2019, Leiyang coal mine flooding accident in 2020, Zhangjiajie 2nd wave of COVID-19 in 2021) (see the Response map in Figure 2 which summarize of selected national and regional emergency response by the Second Xiangya Hospital of Central South University). Second, it is a represented public emergency preparedness center in the Hunan Province which has developed a centralized response system, thereby instilling an emergency response literacy among their staff team. For example, their centralized working model shows great advantages that makes it contain the spread of COVID-19 effectively to support Wuhan city in 2020, e.g., their massive capacity and comprehensive functions, including “fever-clinics” to screen patients, a COVID-19 department to isolate patients, and many makeshift beds as emergency wards. Under several years of team construction and medical rescue training focus, their future preparedness efforts warrant a focus on improving their capacity-building, especially the mental health response and improving their own workforce's well-being. Third, it is a top-ranked tertiary hospital as well as a key national center for healthcare, education, and clinical research in China which has 3,500 beds, 40 clinical departments, and 127 ward areas facing complex healthcare service demands within their regular hospital services in central China which makes them explore the complicated challenges in their practice context. The national simulation centers for experimental teaching and training platform offers an opportunity to design and test this capacity-building project.

**Figure 2 F2:**
[figure not shown]
Response map—summary of selected national and regional emergency response by the Second Xiangya Hospital of Central South University.

#### Trial Participants

This trial will sample frontline healthcare workers, who provide services directly to patients and are the first and often only link to essential health services. The sampling frame includes all professional disciplines of frontline healthcare workers, namely nurses, midwives, doctors, pharmacists, who are employed by the Second Xiangya Hospital of Central South University which is part of the national and regional emergency rescue service in China (i.e., they would be called to provide rescue services to individuals in the event of a disaster or public health emergency).

The eligibility inclusion criteria to participate in the trial are: (A) participants must be over 18 years old; (B) participants are employed in departments that would be called to emergency response (e.g., emergency departments, infectious disease, orthopedic, intensive care unit, etc.); (C) participants are non-mental health frontline healthcare workers. The exclusion criteria to participate in the trial are: (A) they say for whatever reason that they are unavailable to participate in the PFA training course for whatever reason; (B) those who have prior knowledge in related mental health areas (e.g., completed education in a mental health related field or similar training or delivery).

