An appropriate adaption of a psycho-educational intervention is essential to maximize the implementation fidelity and enhance program fit (46). Given evidence on proper PFA adaptation resulting in PFA practice dilution (30), therefore, the adaptation of this Chinese PFA training intervention had been systematically conducted in line with these frameworks, i.e., the ADAPT-ITT cultural adaptation framework combined with the Bernal framework (47, 48). The aspects of language, metaphors, content, concept, goals, methods, and the context, as well as environmental and psychological factors had been well-considered when culturally adapting this training. Throughout this process, stakeholder participation in its development was achieved through: (A) conducting individual interviews (*n* = 15) of healthcare staff to capture their perceived needs (e.g., case range of application context) and training preferences; and (B) conducting three focus groups of frontline healthcare workers (with a total of 33 participants); and (C) using semi-structured discussions with an expert steering group to ensure cultural appropriateness. Drawing on the data collected from these stakeholders, we have identified possible adaptations and refined the PFA training intervention to fit Chinese healthcare practice. Thus, the “Preparing Me” PFA training intervention has been well-tailored to the Chinese frontline healthcare setting (see Table 1 of detailed PFA training intervention content based on TIDieR checklist) (49). Along with the consultation with experts in simulation and clinical education, this adapted Chinese PFA training program include a brief didactic introduction, role-play, case-simulation, and associated learning tools following an interactive and practice-based curriculum design (50–52). These will be delivered over 1-day face-to-face simulation training course (7 h) and two follow-up practice supervision sessions (1 h each); with a focus on improving the trainers' knowledge, skills, and self-efficacy related to support people in acute stress. All six modules comprise didactic information on mental health response to critical incidents and PFA, and each is framed by common challenges in frontline practice to increase its salience and provide practical approaches to implementing PFA into frontline healthcare practice. Training sessions are standardized via the use of a structured trainers' guide including up to 20 trainees. Since prior evidence on 1-day PFA training resulting in inconsistent PFA practice (30), we have added the two follow-up sessions to further support knowledge acquisition and skills development into their clinical practice.

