#### Recruitment

Participants will be recruited from the Second Xiangya Hospital of Central South University through the following two ways: (A) Direct methods: access to research participants will be via two gatekeepers. The first gatekeeper will be the Director of the nursing department in the local hospital, who distribute the study information to the clinical departments managers on behalf of the researcher, (i.e., a communication message/talk based on the email/phone recruitment script). The second gatekeepers will be the clinical department managers who will help to identify the staff in service who are interested in participating and ask them to contact the researcher directly. (B) Indirect methods: Advertisement posters will be posted onto the hospital notice board and be disseminated via social media posts through individual WeChat moments. Participants who are interested in participating will be asked to contact the researchers via a dedicated email address, phone number, and WeChat message.

Once potential participants have expressed an interest in being involved, they will be assessed against the eligibility criteria by the researcher, and if they are eligible, they will then be asked if they have read the participant information sheet. Meanwhile, they will be given an opportunity to ask any questions, and if being addressed in satisfaction, they will be asked to give their written informed consent for participation in the trial. They will be asked to complete the baseline assessments and then randomization to either intervention or control group of the trial will occur.

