#### Randomization

The randomization will be performed by an independent researcher not connected with either participant recruitment or data collection, using a 1:1 ratio as per a computer-generated randomization schedule using randomly permuted block sizes by randomization.com. All eligible participants who give written informed consent will be randomly allocated to either the intervention or control arm of the trial. Due to the nature of the study, only the researcher collecting/analyzing the data from trial participants can be masked to the randomization.

As a check on blindness, the researcher will be asked to guess the group allocation of trial participants after they have completed each final follow-up assessment. Unmasking will not occur until databases are closed and the main analysis has been completed.

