#### Psychoeducation Programme (Control)

Participants in the control arm will receive the best available alternative to PFA training, which in this setting is the hospital's existing 1 day psychoeducation training course. This involves a series of lectures on basic mental health training topics, including the traditional Chinese culture, understanding psychological crisis and skills, referral resources, and ethics.

This study will attempt to minimize contamination between the two arms through (A) engaging different trainers with equivalent clinical and training experience to deliver the training; and (B) consenting participants in both arms will be asked not to share information regarding the training that they have received with colleagues who might be involved in a different arm of the trial.

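### Exclusion criterion (A) checks availability before randomisation for the PFA course only, so clashes with the separate control course can pass screening if the two courses run on different dates

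*Protocol article*

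**What the plan says.** Under Trial Participants, exclusion (A) applies to anyone who reports being "unavailable to participate in the PFA training course for whatever reason". The control course appears in neither the inclusion nor the exclusion criteria.

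Under Recruitment, people who express interest are first screened: "they will be assessed against the eligibility criteria by the researcher". Consent follows, and then: "They will be asked to complete the baseline assessments and then randomization to either intervention or control group of the trial will occur". Under Randomization, allocation is made "using a 1:1 ratio as per a computer-generated randomization schedule".

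Under Psychoeducation Programme (Control), the comparator is the "hospital's existing 1 day psychoeducation training course", taught by different trainers from those in the PFA arm. The PFA arm receives one training day followed by two supervision sessions by WeChat.

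The measures that could be affected are these:

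- Training completion, attendance and dropout are primary feasibility data (Primary Objectives).
- Statistical Data Analysis asks for at least 80% of enrolled trainees to complete all sessions, and for less than 20% missing data at group level at each time point.
- The Conclusions make the main trial depend on 80% retention.
- Under Data Collection, T1 falls immediately after the courses, and the 1- and 3-month measures are collected online.

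**The concern.** An availability check made before allocation works evenly only if it covers whatever the participant may be allocated to. Here it covers one of the two courses. Everyone allocated to PFA has been screened against the course they will attend. Nobody allocated to control has been, as far as the stated criteria go.

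If the timetables differ, two mirror-image people are treated differently. One is free for PFA and rostered on the control date: eligible, randomised, and a likely non-attender if allocated to control. The other is free for the control date and not for PFA: never randomised.

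A feasibility trial exists to learn whether staff attend and supply data. A shortfall in control attendance that came from the screening rule could be read as a fact about the control course, or could count against a progression threshold.

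**Working it through.** **The plan's own figure.** Sample Size gives at least 64 completers after 20% loss: 64 / (1 − 0.20) = 80. The stated N = 80 is reproduced. At 1:1, 80 / 2 = 40 per arm.

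**Order of events.** Eligibility check (PFA availability only), then consent, baseline and randomisation. The check is applied to everyone before allocation, so it selects both arms identically and creates no baseline imbalance. Any difference arises afterwards, when one arm attends a course for which availability was not screened.

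**Timetables.** The article gives no dates for either course. PFA sessions take up to 20 trainees, so 40 / 20 = at least 2 PFA runs, within a recruitment period of 6 weeks. The control course already exists at the hospital. Nothing in the text ties the two timetables together, and nothing says that they differ. The flowchart and the assessment schedule are figures that could not be read.

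**Controls affected.** Let c be the share of controls who clash with their course date. The documents give no value, so c is assumed. Number affected = 40 × c:

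- c = 0 (same dates): 0
- c = 5%: 2
- c = 10%: 4
- c = 20%: 8

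**Effect on attendance.** As an assumed base, take 1 − 0.18 = 82% from the 18% dropout that the article cites from a PFA cluster trial. Suppose that clashes act in the control arm only. Control attendance = 0.82 × (1 − c), and pooled attendance is the mean of the two arms. The last column is the 95% half-width for the difference, 1.96 × √(p₁(1 − p₁)/40 + p₂(1 − p₂)/40).

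| c | Control | Gap (points) | Pooled | Half-width (points) |
|---|---|---|---|---|
| 0 | 82.0% | 0 | 82.0% | 16.8 |
| 5% | 77.9% | 4.1 | 79.95% | 17.5 |
| 10% | 73.8% | 8.2 | 77.9% | 18.1 |
| 20% | 65.6% | 16.4 | 73.8% | 18.9 |

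If completion is pooled over arms, which the article does not specify, it falls below 80% when 0.82 × (1 − c/2) < 0.80, that is, when c > 2 × (1 − 0.80/0.82) = 4.9%.

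**Effect on T1 completeness.** If none of 8 clashing controls supplied T1 data, the control arm would have 8 / 40 = 20% missing. That already fails a strict limit of less than 20% if the limit is applied by arm. Over all 80 participants it would be 8 / 80 = 10%. Both figures assume that a person who misses the course also misses T1, which the article does not say.

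**The case against.** The strongest reply is that the mechanism needs different dates, and the article never states them. Different trainers for the two arms would fit parallel sessions equally well, and course calendars are the sort of detail that a condensed article leaves out. That stands, and it makes the point conditional. It does not remove it, because the criterion itself is stated and names one course.

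Other replies also have force:

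- A reader might infer that no PFA participant would miss the course for scheduling reasons. The documents do not support that. Saying that one is available does not guarantee attendance among staff who can be called out to emergencies, and the PFA arm carries the extra supervision sessions. The direction of the net attendance difference is therefore unknown.
- A reader might infer that retention is biased between arms. The 1- and 3-month measures are online and do not depend on having attended a course.
- A reader might infer that estimates of effect are biased. That would also require roster clashes to be related to outcome, and nothing in the article suggests it.
- The 80% thresholds are not stated by arm, no between-arm comparison of attendance or retention is specified, and even the 16.4-point gap lies within its half-width of 18.9 points.

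The last reply limits the consequence but does not dispose of the point. Sampling error is no defence of an avoidable systematic shift, and thresholds judged on observed proportions can be crossed without any test.

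**Conclusion.** The point holds in conditional form and is minor. Availability is screened for one arm's course only. If the course dates differ, control attendance, and possibly T1 completeness, may be lower for scheduling reasons alone: about 2 to 8 of 40 controls at assumed clash rates of 5% to 20%, and none if the dates coincide. Those rates are illustrations without a source in the documents. The claim that attendance and retention are in fact biased between the arms would go beyond what the article shows.

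**What to change.** Reword exclusion (A) so that a participant must be available for either course on its scheduled date. Alternatively, run both courses on the same dates. In either case, fix the dates before each batch is randomised. With a symmetric check, the expected attendance gap from this source is zero, and N = 80 with 64 completers is unchanged.

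The cost is one more date on the screening form, and a few staff who wait for a later batch or are excluded. Deferral is preferable to exclusion, because the article also asks for at least 90% screening eligibility: if everyone else were eligible, excluding 10% for a control-course clash would put the rate at exactly 90%. Running both courses on the same dates avoids this, but requires wards to release both arms at once. The change has to be made before the first randomisation.
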